### Outcomes and Measurement

The study’s primary outcome is dual HBV and HCV test uptake, defined as the proportion of participants who tested for HBV and HCV verified by hospital records. Secondary outcomes will include (1) HBV and HCV positivity rate, defined as the proportion of participants that tested positive; (2) donation rates and amounts, defined as the proportion of participants who donated and the total amount donated; and (3) cost-effectiveness analysis, defined as the test incremental cost-effectiveness ratio of the PIF model compared to the control arm. Prespecified subgroup analysis will compare HBV and HCV test uptake rates between PIF and the control arms by nationality, gender (male vs female), age (≤30 y vs >30 y), and level of education. Further details are summarized in Table 1 below.

**Table 1. T1:** Primary and secondary outcomes with definitions.

Indexes	Definition
Primary outcome	
HBV^a^ and HCV^b^ test uptake	The proportion of participants who tested for HBV and HCV as verified by hospital records
Secondary outcome	
HBV and HCV positivity rate	The proportion of participants who tested positive
Donation rates and amounts	The proportion of participants who donated to others for HBV and HCV testing, and the total amount donated
Cost-effectiveness analysis	The test incremental cost-effectiveness ratio of the pay-it-forward (PIF) model compared to the control arm

a HBV: hepatitis B virus.

b HCV: hepatitis C virus.

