### Sample Size

In a pretest study conducted from April 1 to May 27, 2024, among 20 international migrants from LMICs in Guangzhou, we observed a 90% (9/10) HBV and HCV test uptake rate in the PIF arm and 0% (0/10) in the control arm. However, we adopted the anticipated test rate from another study that applied the PIF strategy to promote HBV and HCV testing among MSM in China (59.4% in the intervention arm and 25.3% in the control arm) to ensure a stable result. Accordingly, we anticipated that 59.4% of participants would accept the dual HBV and HCV testing in the intervention arm and 25.3% of patients would accept testing in the control arm. Based on a 2-sided *t* test (unpooled), an intracluster correlation of 0.10, and an alpha of .05, an anticipated 10 clusters (consisting of approximately 5 participants per cluster) are needed in each intervention arm for the study to achieve an 80% power, resulting in a total sample size of 100 participants.

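### Nationality subgroups cannot be compared between arms as tabulated, and the other subgroups are too imprecise to be read by significance within each level

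*Protocol article*

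**What the plan says.** Outcomes and Measurement in the Protocol article states: "Prespecified subgroup analysis will compare HBV and HCV test uptake rates between PIF and the control arms by nationality". The same sentence goes on to gender, age with a cut at 30 years, and education. It gives no categories for nationality or education. The sentence describes a comparison of arms and does not mention comparing effects between levels.

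Sample Size powers only the overall comparison, at "59.4% in the intervention arm and 25.3% in the control arm", with "an intracluster correlation of 0.10, and an alpha of .05". It concludes that "an anticipated 10 clusters (consisting of approximately 5 participants per cluster) are needed in each intervention arm", for 100 participants in all.

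Data Analysis specifies generalized estimating equations (GEE) with a logit link for the arm comparison. Table 2 in Results gives the enrolled counts by arm for sex, age band, education and region.

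**The concern.** Two problems follow once the subgroup sentence is set beside Table 2.

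- **Nationality.** Two of the four regions have no PIF participants, so no between-arm estimate exists there. A third has two controls. A split by country could only be sparser.
- **The other factors.** The levels differ in size. When arms are compared separately within levels of unequal size, the larger level tends to reach significance and the smaller does not, even if the effect is identical.

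Future Directions and Dissemination says the findings will inform tailoring of the intervention and a larger trial. A conclusion that PIF works only in men, or only in African migrants, could therefore be carried forward when it reflects nothing but subgroup size.

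**Working it through.** **The plan's own figure.** Inputs from Sample Size: p1 = 0.594, p2 = 0.253, difference d = 0.341, ICC 0.10, cluster size 5.

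- Design effect = 1 + (5 − 1) × 0.10 = 1.4.
- Unpooled standard error with K clusters per arm = √{[p1(1 − p1) + p2(1 − p2)] × 1.4 / (5K)}, where p1(1 − p1) = 0.2412 and p2(1 − p2) = 0.1890.
- A noncentral t with 2(K − 1) degrees of freedom gives 79.0% power at K = 9 and 83.6% at K = 10.

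Ten clusters per arm is the smallest number that reaches 80%, so the overall sample size is reproduced.

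**Subgroups.** The counts are from Table 2, and the planned rates are assumed to hold in every subgroup. For n1 PIF and n2 control participants:

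- 95% CI half-width = 1.96 × √[0.2412/n1 + 0.1890/n2].
- Approximate power = Φ(0.341/SE − 1.96).
- Exact power = total binomial probability of all results with two-sided Fisher P < 0.05.

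Clustering is ignored here. A design effect of 1.4 widens the intervals by √1.4, about 18%.

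| Subgroup | PIF v control | Approximate power | Exact power | CI half-width (points) |
|---|---|---|---|---|
| Africa | 44 v 43 | 93% | 88% | 20 |
| Southeast Asia | 6 v 2 | 15% | 2.5% | 72 |
| South Asia | 0 v 2 | none | none | no estimate |
| Others | 0 v 3 | none | none | no estimate |
| All non-African | 6 v 7 | 26% | 15% | 51 |
| Men | 35 v 38 | 88% | 82% | 21 |
| Women | 15 v 12 | 48% | 35% | 35 |
| High school and below | 16 v 14 | 52% | 38% | 33 |
| Some college or vocational | 15 v 12 | 48% | 35% | 35 |
| Bachelor's and above | 19 v 24 | 66% | 54% | 28 |

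An odds ratio from the logit model fails if everyone or no one in an arm is tested. At the planned rates the chance of this is 64% in Southeast Asia and 17% in all non-Africans. It is about 3% or less for sex and education.

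**Chance that exactly one level is significant under a uniform effect.** With powers A and B in the two levels, this is A(1 − B) + B(1 − A).

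- Sex, approximate: 0.879 × 0.519 + 0.481 × 0.121 = 0.51.
- Sex, exact: 0.824 × 0.653 + 0.347 × 0.176 = 0.60.
- Africa v other, approximate: 0.929 × 0.740 + 0.260 × 0.071 = 0.71. With design effect 1.4 it is 0.70.
- Africa v other, exact: 0.880 × 0.848 + 0.152 × 0.120 = 0.76.

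**What an interaction estimate can detect.** Its standard error is the root of the summed variances of the two subgroup differences.

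- Sex: √(0.01186 + 0.03183) = 0.209. For 80% power the effects must differ by about 2.8 × 0.209 = 0.59, or 59 points.
- Africa v other: √(0.00988 + 0.06719) = 0.278. The effects must differ by about 2.8 × 0.278 = 0.78, or 78 points.

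**The case against.** The subgroup sentence is brief. It names no test and no decision rule, and it does not rule out an interaction term in the GEE. Merging of sparse categories and choice of test are usual content of a statistical analysis plan, which is not shown. That stands as far as it goes: the silence on interaction is not itself a fault. What remains is the comparison the article does describe, set against its own counts.

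Three stronger readings are tempting, and the document does not support them.

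- **All the subgroups are empty or tiny.** Only nationality fits. Every level of sex and education has 12 to 38 people per arm, and an estimate is expected at the planned rates.
- **The analysis will produce false subgroup differences.** That happens only if significance is read level by level, and the article does not say it will be.
- **The age cut contradicts Table 2.** The plan fixes "age (≤30 y vs >30 y", while Table 2 uses 18–35, 36–45 and over 45. Descriptive bands need not match a subgroup cut. The number aged 30 or younger is not shown; it is at most 13 v 16. Replacing a prespecified cut after baseline data would weaken prespecification.

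The normal approximation is also rough in cells as small as 6 v 7, which is why exact figures are shown beside it. Applying the full design effect of 1.4 within each sex raises the sex figure to 57%. It probably overstates clustering, because splitting clusters by sex makes them smaller. If the sexes mix at random, the design effects are 1 + 4 × 0.73 × 0.10 = 1.29 for men and 1 + 4 × 0.27 × 0.10 = 1.11 for women, and the figure is about 53%. Neither changes the conclusion.

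**Conclusion.** The point holds in limited form. Nationality cannot be compared between arms in the regions tabulated, because two have no PIF participants and a third has two controls. Table 2 does not declare these regions to be the subgroup definition, but the article gives no other. The remaining subgroups are estimable and imprecise. Reading them by within-level significance would give discordant results about 51% to 60% of the time by sex, and 70% to 76% for Africa v other, with no real difference in effect.

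These figures assume that the planned rates apply in every subgroup and that the two levels are independent. If control uptake is closer to the pretest, where "we observed a 90% (9/10) HBV and HCV test uptake rate in the PIF arm and 0% (0/10) in the control arm", odds ratios could fail in many subgroups for that reason rather than because of subgroup size. The trial is sized only for the overall comparison, and its primary conclusion does not depend on this point.

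**What to change.** - For each factor, report the arm-by-subgroup interaction estimate with a 95% CI from the GEE, together with the subgroup estimates and their CIs. Label them exploratory, and do not interpret P values within levels.
- Collapse nationality to Africa (44 v 43) v other (6 v 7). Disclose that this grouping was set after baseline data, and say whether outcomes had been seen. The article reports that descriptive analysis was partly complete and that uptake results will appear separately; it does not show that outcomes were still unseen.
- Say in advance what will be shown if an arm in a subgroup is all or none tested, for example counts alone.
- Keep the age cut at 30. Age in years may be added as a supplementary analysis.

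The cost is a change of wording in the analysis plan; no new data are needed. The downside is low power. Interactions would have to be about 59 points by sex or 78 points for Africa v other to be detected with 80% power, and the non-African estimate would still carry a CI of about ±51 points (±60 with design effect 1.4). The report should say so, and should not take a non-significant interaction as evidence of a uniform effect.

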### Sample Size

In a pretest study conducted from April 1 to May 27, 2024, among 20 international migrants from LMICs in Guangzhou, we observed a 90% (9/10) HBV and HCV test uptake rate in the PIF arm and 0% (0/10) in the control arm. However, we adopted the anticipated test rate from another study that applied the PIF strategy to promote HBV and HCV testing among MSM in China (59.4% in the intervention arm and 25.3% in the control arm) to ensure a stable result. Accordingly, we anticipated that 59.4% of participants would accept the dual HBV and HCV testing in the intervention arm and 25.3% of patients would accept testing in the control arm. Based on a 2-sided *t* test (unpooled), an intracluster correlation of 0.10, and an alpha of .05, an anticipated 10 clusters (consisting of approximately 5 participants per cluster) are needed in each intervention arm for the study to achieve an 80% power, resulting in a total sample size of 100 participants.

### Data Collection and Measures

The study survey will be hosted on the Wenjuanxing platform (Ranxing), a web-based survey tool that meets industry standards for security and functionality [30]. The English, French, and Chinese versions of the questionnaire will be available to participants. To ensure questions are clear and culturally appropriate, the surveys were pretested with 5 English-native-speaking migrants, 5 Chinese natives, and 2 French-speaking migrants, who provided feedback used to revise the questionnaire and optimize the survey process (Figure 1).

**Figure 1. F1:**
[figure not shown]
Flowchart showing the study design and recruitment process. HBV: hepatitis B virus; HCV: hepatitis C virus; LMIC: low- and middle-income country; PIF: pay-it-forward.

The questionnaire includes four domains: (1) sociodemographic characteristics, (2) medical service use, (3) knowledge of HBV and HCV prevention, and (4) sexual behavior. Sociodemographic characteristics data will include age, country of origin, reasons for travel to China, level of education, monthly income after tax, and religious beliefs. Additional data will include previous chronic and transmissible disease diagnoses, medical service use experiences in China, and barriers to seeking health care in China. Seven questions will assess participants’ knowledge about HBV and HCV transmission, infection symptoms, HBV vaccine, and prevention measures. The survey will also collect data on participants’ sexual behaviors, like the number of regular and casual sexual partners, condom and drug use rates, and knowledge of the HBV and HCV status of sexual partners.

Participants can complete the surveys online by using WeChat or offline by completing the paper-based questionnaire. WeChat is a multipurpose social media smartphone app with messaging, multimedia, and financial functionality. There were over 1 billion monthly active users on WeChat in the first half of 2024 [31]. A project-dedicated iPad will also be provided for participants without a smartphone or WeChat account who opt to complete the questionnaire online. Printed copies of the survey will be provided to participants who prefer to answer offline. The physician and a research assistant will be available to assist participants and clarify questions as needed.

### Incentives and Reimbursement

Participants who complete the questionnaire will receive US $4.13 (30 RMB) as an incentive for their time. There will be no treatment cost reimbursements for participants who test positive for HBV and HCV and receive treatment at the study site. The free HBV and HCV test, valued at about US $5.91 (43 RMB), will only be provided to participants in the intervention arm.

### Data Analysis

Sociodemographic characteristics, sexual behavior, and HBV and HCV prevention knowledge data will be analyzed descriptively, and nominal variables will be tested using the *χ*^2^ test to compare differences between PIF and control group participants. The absolute proportions of dual HBV and HCV testing will be compared between the PIF and control groups using generalized estimating equations with a logit link, accounting for clustering effects. We will evaluate whether the PIF intervention is superior to the control arm in increasing HBV and HCV testing uptake rates by 20%. Multivariable models will adjust for potential confounders, including key sociodemographic factors and a previous STI diagnosis, selected a priori based on prior literature and theoretical relevance. Additional covariates associated with testing uptake in bivariate correlation (*P*<.20) will also be considered for inclusion in the final model to minimize residual confounding. Sensitivity analyses will also be conducted to assess the robustness of intervention effect estimates under alternative correlation structures, ensuring appropriate estimation even with modest cluster sizes. A complete-case analysis will be conducted if the primary outcome is missing for fewer than 15% of participants. If missingness in the primary outcome is ≥15% and determined to be random, multiple imputation will be applied.

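### The analysis section asks whether uptake is superior by 20%, but the sample size was computed against zero difference, and the scale and role of the 20% are not stated

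*Protocol article*

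**What the plan says.** The protocol article touches the primary comparison in three places.

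- **Study Design** states the hypothesis as plain superiority of PIF over standard services in increasing testing. It gives no threshold.
- **Sample Size** anticipates "59.4% in the intervention arm and 25.3% in the control arm". The method is given as "Based on a 2-sided *t* test (unpooled), an intracluster correlation of 0.10, and an alpha of .05", and the result is that "an anticipated 10 clusters (consisting of approximately 5 participants per cluster) are needed in each intervention arm" for 80% power, 100 participants in total. No margin or non-zero null value appears.
- **Data Analysis** says: "The absolute proportions of dual HBV and HCV testing will be compared between the PIF and control groups using generalized estimating equations with a logit" (the link function), allowing for clustering. The next sentence reads: "We will evaluate whether the PIF intervention is superior to the control arm in increasing HBV and HCV testing uptake rates by 20" (percent). It does not say whether the 20% is absolute or relative, or whether it is a null value, a target effect or a benchmark.

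**The concern.** The hypothesis and the power calculation refer to a zero difference, while the analysis section refers to superiority by 20%. If the 20% is a margin that the trial must beat, the 80% power was calculated for a different and easier test.

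The practical risk is in the conclusion. Suppose the trial performs exactly as planned, with an observed difference of 34.1 points and a 95% confidence interval of about 11 to 57 points. That interval excludes 0 but not 20. The same result could be called a success or a failure, and nothing in the article settles which. An unclear criterion for the primary outcome leaves the choice open until the data have been seen.

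**Working it through.** **Inputs.** From Sample Size: p1 = 0.594, p2 = 0.253, difference 0.341; ICC 0.10; cluster size m = 5; K = 10 clusters per arm; 2-sided alpha 0.05; t test with unpooled variance. From Data Analysis: 20%, scale not stated.

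**Standard error**
- Design effect = 1 + (5 − 1) × 0.10 = 1.4.
- Variance terms: 0.594 × 0.406 + 0.253 × 0.747 = 0.2412 + 0.1890 = 0.4302.
- SE = √(0.4302 × 1.4 / 50) = 0.1097, or 10.97 points.
- Critical t with 2K − 2 = 18 df: 2.101.

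**Step 1. Reproduce the plan's figure (null difference 0)**
- K = 10: noncentrality 0.341 / 0.1097 = 3.107; power 83.6%.
- K = 9: power 79.0%.
- Ten clusters per arm is therefore the smallest number reaching 80%, as stated. The sample size follows from a zero null, with no margin in it.

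**Step 2. Absolute 20-point margin (null difference 0.20)**
- Noncentrality (0.341 − 0.20) / 0.1097 = 1.285; power 22.9% (25.0% by the normal approximation).
- For the lower 95% limit to clear 20 points, the observed difference must exceed 0.20 + 2.101 × 0.1097 = 0.431, about 43 points.
- 80% power would need 49 clusters of 5 per arm, about 490 participants.
- Smaller clusters do not change this: with 50 per arm, power is about 29% for clusters of 2 and 32% for independent participants.

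**Step 3. Relative 20% margin (uptake ratio above 1.2)**

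| Method | Power, t (18 df) | Power, normal |
|---|---|---|
| Log ratio: SE 0.319, noncentrality 2.10 | 51% | – |
| p1 − 1.2 × p2 tested against 0 | 63% | 68% |
| Fixed margin 0.2 × 25.3% = 5.1 points | 71% | 75% |

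The range is about 51% to 75% with clusters of 5. With clusters of 2, the fixed 5.1-point version rises to about 83%.

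**Step 4. A true 20-point rise tested against zero (25.3% to 45.3%)**
- SE = √[(0.453 × 0.547 + 0.1890) × 1.4 / 50] = 0.1106; noncentrality 0.20 / 0.1106 = 1.81; power 40% (44% normal).

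**Step 5. A minimum observed increase of 20 points, in addition to significance against zero**
- At the planned SE, significance already needs an observed difference of 2.101 × 0.1097 = 0.231, about 23 points.
- The 20-point condition therefore adds nothing, and power stays at 83.6%.

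**Interval in the planned scenario.** 0.341 ± 2.101 × 0.1097 gives 0.110 to 0.572.

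**The case against.** The strongest objection is that the article contains no shifted-null test. The Data Analysis sentence gives no null value, no rule about a confidence limit and no mention of a margin. It says only that the team will evaluate the question, and it follows a sentence describing an ordinary GEE comparison. Study Design and Sample Size both fit a zero null. On that view the 20% is a loose benchmark, and under the reading in Step 5 no power is lost. A full analysis plan may also define the term.

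Much of this stands. A reader might infer that the trial has only 23% power for its primary test, or that a trial performing as planned will probably be declared a failure. The documents do not support either statement. Both need the 20% to be absolute, to be the null value, and to be judged by the lower 95% limit, and none of these is written. The preceding sentence speaks of absolute proportions, which makes the absolute scale the more natural reading, but it does not fix the role of the 20%. Nor is the sample size miscalculated; it reproduces.

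What does not stand is that the sentence is harmless. It says superior by 20%, and the benchmark reading has to be supplied by the reader. The point is not a missing detail: the article states a criterion that does not match its own hypothesis and power statement. The pretest rates (90% versus 0%) would clear any of these margins, but the Sample Size section set them aside in favour of 59.4% and 25.3%.

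**Conclusion.** The mismatch is real. The 20% enters neither the hypothesis nor the sample size, and the sentence introducing it fixes neither scale nor role. At the plan's own inputs, power ranges from about 23% (absolute margin) to about 84% (benchmark in addition to significance). A relative margin gives about 51% to 75%, and detecting a true 20-point rise about 40%. The 80% claim holds for the zero-difference test, and for the 20% sentence only if it adds nothing to that test.

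These figures assume 59.4% versus 25.3%, ICC 0.10, and 10 equal clusters of 5 per arm analysed with 18 df. The 23% is the least favourable of the readings considered and should not be quoted as the trial's power.

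The point matters because it governs how the primary result will be declared. It does not call the size of the trial for a zero-difference test into question.

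**What to change.** Issue a dated, disclosed clarification before uptake is analysed by arm. Suggested content: *The primary test is of H0: risk difference = 0, 2-sided at 5%, reported with a 95% confidence interval. An increase of 20 absolute percentage points is a benchmark for interpreting that interval and is not a success criterion.*

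If 20% is kept as the success margin, state its scale and restate the power for it at 59.4% versus 25.3% (about 23% if absolute).

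Dating and disclosure matter because the Results section reports that recruitment ended in February 2025, that data were cleaned by September 2025 and that parts of the descriptive analysis were complete by the end of December 2025. The article does not show whether uptake by arm has been examined. If it has, report the result against both zero and 20 points and say when the clarification was made.

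The cost is a sentence or two in the analysis plan and a line in the results paper. No further participants are needed.

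### The adjusted model may take in covariates because of their observed association with the primary outcome (P<.20), with no retention rule and no statement of which model carries the superiority conclusion

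*Protocol article*

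**What the plan says.** All of the relevant text is in the Data Analysis section of the protocol article, in this order:

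- Dual testing is compared between arms "using generalized estimating equations with a logit link, accounting for clustering effects". No covariates are named.
- The aim is to judge whether pay-it-forward is "superior to the control arm in increasing HBV and HCV testing uptake rates by 20" per cent.
- Multivariable models follow. Their core set is key sociodemographic factors and a previous STI diagnosis, "selected a priori based on prior literature and theoretical relevance".
- The set is then widened: "Additional covariates associated with testing uptake in bivariate correlation", with a threshold of P<.20, "will also be considered for inclusion in the final model to minimize residual confounding".

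Outcomes and Measurement makes dual HBV and HCV test uptake the primary outcome. The screen is therefore run against the variable that the trial is designed to compare. Data Collection and Measures describes the pool from which candidates could come: "The questionnaire includes four domains: (1) sociodemographic characteristics, (2) medical service use, (3) knowledge of HBV and HCV prevention, and (4) sexual behavior".

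**The concern.** Clusters are randomised, so baseline differences between arms are due to chance unless allocation fails. Screening on the outcome is a poor remedy for either problem. It also lets the trial data help decide which adjusted treatment effect is estimated.

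Two gaps make this matter. Being considered for inclusion is not a retention rule, so two analysts could follow the text and fit different models. And the text does not say which model supports the superiority claim. The choice is live, because the Results section already reports arm differences at P=.03 for income and for region.

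Selection could also change the analysed sample. In Table 2, two partner-related variables have answers from only 33 + 38 = 71 of 100 participants. If one of them passed the screen and entered without a category for the rest, a standard fit would drop 29 people.

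**Working it through.** **1. The plan's own sample size.** The inputs come from the Sample Size section: 59.4% v 25.3%, 10 clusters of about 5 per arm, "an intracluster correlation of 0.10, and an alpha of .05".

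- Design effect: 1 + (5 − 1) × 0.10 = 1.4.
- Unpooled variance: 0.594 × 0.406 + 0.253 × 0.747 = 0.4302.
- Standard error with 50 per arm: √(0.4302 × 1.4 / 50) = 0.1097.
- Noncentrality: 0.341 / 0.1097 = 3.11, on 2 × (10 − 1) = 18 degrees of freedom.
- Power is 83.6% with 10 clusters per arm and 79.0% with 9.

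Ten is the smallest number that reaches 80%, so the stated figure reproduces. Expected testers are 50 × 0.594 + 50 × 0.253 = 29.7 + 12.65, about 42.

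**2. The candidate pool.** Data Collection and Measures names about 15 variables or topics, or about 21 if the seven knowledge questions are screened singly. Some belong to the a priori set. The number screened is not stated, so 5 to 20 candidates were assumed.

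**3. The screen reacts to the treatment effect.** Take the income split in Table 2 (17/18/15 v 8/17/25), the planned uptake rates, no effect of income, and no clustering. Expected uptake by income group is then:

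- lowest: (17 × 0.594 + 8 × 0.253) / 25 = 48.5%
- middle: (18 × 0.594 + 17 × 0.253) / 35 = 42.8%
- highest: (15 × 0.594 + 25 × 0.253) / 40 = 38.1%

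Income passes P<.20 in about 28% of simulated trials, against about 20% with no treatment effect. Part of what the screen detects is the treatment effect seen through a chance imbalance.

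**4. Type I error, small-sample reference.** Simulation with no treatment effect: N=100, ICC 0.10, uptake 42%, logit GEE with independence working correlation and a cluster-robust standard error, t reference on clusters minus 2 degrees of freedom. Four a priori covariates were assumed, none affecting uptake, with about 8,000 replicates per setting. The last column lets the analyst keep any subset of the screened covariates (search limited to five of them) and report the most favourable model.

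| Setting | A priori only | Plus all at P<.20 | Unadjusted or screened, either may be claimed | Best subset |
|---|---|---|---|---|
| 20 clusters of 5, 10 candidates, uncorrelated within cluster | 5.0% | 5.2% | 6.3% | 6.7% |
| 20 of 5, 10 candidates, within-cluster correlation 0.3 | 5.0% | 5.5% | 6.8% | 8.5% |
| 20 of 5, 20 candidates, correlation 0.3 | 5.4% | 6.7% | 8.4% | 13.0% |
| 50 of 2, 10 candidates, correlation 0.3 | 5.4% | 5.8% | 6.8% | 7.7% |

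The mechanical screen adds about 0.3 to 1.3 points (first row 0.3 before rounding). Free choice of subset adds 6.7 − 5.0 = 1.7 up to 13.0 − 5.4 = 7.6 points, that is, about 2 to 8. The Monte Carlo standard error is about 0.25 points on each rate.

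**5. Type I error, uncorrected robust z test.** 20 clusters of 5, five a priori and nine screened covariates assumed, about 4,000 replicates per setting.

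| Setting | Unadjusted | A priori only | Plus screened |
|---|---|---|---|
| Uptake 25.3%, uncorrelated | 6.8% | 7.7% | 8.2% |
| Uptake 25.3%, correlation 0.3 | 6.8% | 8.9% | 10.0% |
| Uptake 15%, uncorrelated | 7.2% | 8.4% | 9.4% |
| Uptake 15%, correlation 0.3 | 7.2% | 9.9% | 11.5% |

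From unrounded rates, the screen adds about 0.6 to 1.5 points. The unadjusted test already exceeds 5% by about 2 points, and the a priori covariates add a further 0.9 to 2.7. Both of those come from a robust z test with 20 clusters, not from the P<.20 rule.

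**The case against.** The strongest defence is the order of the text. The between-arm comparison comes first and names no covariates, the superiority statement follows, and only then do multivariable models appear. Their core set is fixed a priori, and the screen concerns extra covariates only. On that natural reading the headline result never meets the screen. This largely stands: a reader might infer that the main effect will depend on covariates chosen after uptake is seen, but the article does not say so. What survives is that it does not rule this out, because it speaks of a final model and never names the primary one.

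A reader might also infer that the screen is a major source of false positives. The calculations do not support that when the rule is applied mechanically. Comparing an unadjusted model with one holding both forced and screened covariates would credit the screen with inflation that mostly arises elsewhere. Nor does the article settle whether a small-sample correction will be used, which an analysis plan may cover.

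Two further inferences should not be pressed. The article does not say that the screening tests ignore clustering; it mentions only bivariate correlation. And with a logit link, the conditional odds ratio changes with any prognostic adjustment, including a fixed list, so that feature is not peculiar to screening.

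**Conclusion.** The point holds in a limited form. The stated rule lets the primary outcome help choose the adjusted model, gives no retention rule, and leaves open which model decides superiority. The adjusted estimate is therefore not prespecified, and the reason given for the rule does not fit a randomised comparison.

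The type I error cost over the fixed a priori set is about 0.3 to 1.5 percentage points if the rule is applied mechanically, and about 2 to 8 points if the analyst may choose among the models it permits. These figures rest on assumptions that the article does not supply: four or five a priori covariates, 9 to 20 screened candidates in the runs shown, within-cluster covariate correlation of 0 to 0.3, and covariates unrelated to uptake. A run with prognostic covariates showed the same pattern. Larger inflation belongs to the small-cluster question. This is something the plan should change, but not evidence that the main result will be wrong.

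**What to change.** Before uptake by arm is examined:

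1. Name the covariate-free, cluster-respecting GEE comparison as the primary analysis that carries the superiority conclusion.
2. Keep one adjusted model as a sensitivity analysis, with a short fixed list drawn from the a priori set and used whatever its association with uptake.
3. Delete the P<.20 step, or label any model that uses it exploratory.

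The Results section says that recruitment has ended, the data are cleaned and uptake results will be published separately. It does not say whether uptake by arm has been seen. If it has, the change should be dated and disclosed. The list should rest on prior knowledge rather than on the imbalances already reported.

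The cost is one sentence deleted and one list written, with no new data. The small downside is that a prognostic covariate outside the list would go unadjusted.
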